### Recruitment

A total of 12 patients with OI type I will be recruited at a tertiary orthopedic hospital. Given that this study will be conducted remotely, patients who meet the study eligibility criteria will be contacted by the study coordinator over the phone. Those who are interested in participating will receive a follow-up email from the study coordinator with the appropriate consent or assent form, providing them with more information regarding their participation. Based on participant’s preference, consent or assent forms will be either emailed or mailed to their place of residence. To ensure privacy, all emails from the study coordinator will be sent encrypted. Study participants will be randomized into either (1) the supervised group or (2) the follow-up group. Study personnel will produce a block randomization list using a random number generating software, which will be sent to the principal investigator. Each randomized number will be written on piece of paper and placed in an envelope. Once a study participant is enrolled, a hospital employee who is not involved in the study will select one of the envelopes and deliver it to the study personnel, who will assign the study participant to the specified group.

### Evaluations and Intervention

#### Overview

The duration of the study is 16 weeks: 12 weeks for the intervention and 2 weeks at the beginning and end for evaluations. All participants will be given an exercise program to be completed at home. Both groups will use the teleconferencing application Microsoft Teams (version 1.3.00.28, Microsoft Corp). The supervised group will be monitored every session, while the follow-up group will receive feedback every 4 weeks.

Previous to the intervention, participants will be provided with initial testing and tutorials on the telemedicine application (Microsoft Teams) and the activity and heart rate monitor (Polar A370 watch; Polar Electro). Participants will be mailed the required equipment, such as the Polar A370 activity monitor (Polar watch), a 5-pound exercise ball, and a resistance band. All attempts possible have been made to ensure this study uses a minimal amount of equipment in order to reach a larger population that may have limited access to resources while also ensuring no sacrifices are made to the overall quality of the study. Both video and written instructions in English and French will be available to participants throughout the study. Instructions for the following will be included: telemedicine connections, completion of questionnaires, and Polar watch details (Bluetooth and USB connections, charging, and data transfer). Additionally, all study participants will have access to the 12-week exercise plan throughout the entire study. The exercise plan includes an illustration, video, and written description of each exercise, as well as 2 easier and 2 more difficult modifications for each movement (Figure 1). The exercise plan comprises 6 warm-up exercises, 7 to 8 exercises that will be repeated 3 times, and 5 cool-down stretches.

**Figure 1 figure1:**
[figure not shown]
Home-exercise program instructions.

#### Evaluations

##### Overview

To assess the impact of the 12-week exercise program, a comparison of pre- and postintervention evaluations will take place (Table 1). The pre- and postintervention evaluations will be recorded on Microsoft Teams in order to better assess and compare participants’ progress before and after the intervention. Throughout the evaluations, study personnel will ask participants to have a parent or caregiver supervising nearby. During the pre- and postintervention evaluations, participants will be asked to complete the following three Patient-Reported Outcomes Measurement Information System (PROMIS) questionnaires: (1) Mobility Short Form, (2) Pain Interference Short Form, and (3) Physical Activity Short Form. Previous research has shown that PROMIS questionnaires have been successfully validated and are clinically feasible for a pediatric population [14]. These questionnaires will establish a baseline indicator for participant’s pain, mobility, and physical activity levels previous to the intervention. Participant's pre- and postintervention questionnaires will be compared to determine what changes, if any, were realized by the participant.

**Table 1 table1:** Pre- and postintervention evaluation tests.

Test	Assessment	Parameter
Sit-to-stand test	Cardiopulmonary fitness and lower body muscular strength	Heart rate (beats per minute) and total number of repetitions performed
Single-legged balance test	Visual and proprioceptive inputs	Time (seconds)
Push-up test	Upper body muscular endurance	Total number of repetitions performed
Sit-up test	Abdominal strength	Total number of repetitions performed
Heel-rise test	Lower body muscular endurance	Time (seconds)

##### Sit-to-Stand Test

The sit-to-stand test assesses cardiopulmonary fitness and lower body muscle strength [15,16]. The participant will sit down and stand up from a chair with their hands on their hips as many times as possible within 1 minute. The participant’s heart rate (in beats per minute) will be taken immediately before, during, and after the test, which will be measured on the Polar A370 heart rate monitor. The number of repetitions completed will be recorded at the end of the test and expressed in absolute value [16]. Additionally, the number of completed repetitions will be expressed as the product of body weight to provide an index of total work (repetitions × weight in kg) [16,17].

##### Single-Legged Balance Test

Postural control will be assessed with 2 visual conditions: eyes open and eyes closed. The participant will stand on 1 leg with their arms crossed over their chest for up to 45 seconds. The participant will complete both visual conditions on each foot. Throughout the test, study personnel will ask the participant’s parents or caregivers to stand close by for support in case the participant loses their balance. The duration of time the participant can maintain their balance under each condition will be collected [7].

##### Push-Up Test

The push-up test assesses upper-body muscular endurance of the chest, shoulders, and arms. The participant will perform as many consecutive push-ups as they can with no time limit. The test will be stopped if the participant is unable to maintain proper technique over 2 consecutive repetitions. Following the Canadian Society of Exercise Physiology, Physical Activity Training for Health (CSEP-PATH) guidelines, female participants will use their knees as their pivot point, whereas male participants will use their toes as their pivot point [7].

##### Sit-Up Test

The sit-up test will evaluate abdominal strength. The participant will complete as many sit-ups as they can within 1 minute. The participant will rise to a seated position from lying down with their knees bent and their arms crossed over their chest [7].

##### Heel-Rise Test

The heel-rise test evaluates muscular endurance of the lower limbs [18]. The participant will complete 2 trials of raising their heels 20 times in a row, as fast as possible, with their arms crossed over their chest. Participants will be given a rest period of 2 minutes between the 2 trials. Ankle plantar flexor strength is scored from 0 to 5, based on the number of heel rises the participant is able to complete [18].

#### Exercise Intervention

The exercise intervention will begin with 35 minutes twice a week, including a warmup and cooldown, each 5 minutes in duration. Every 4 weeks, the training will intensify in either duration of exercise or number of sessions per week, which is required to stimulate physiological adaptation and enhance improvement [7]. For the duration of the intervention, a kinesiologist (human movement specialist) will provide training and supervision to participants in the supervised group at home through live video sessions. Participants in the supervised group will be separated into 2 groups of 3 participants. For the follow-up group, the kinesiologist will meet with participants individually every 4 weeks to review their progress, preview the next month’s exercise plan, and address any concerns or challenges the participants may have. The exercise program timelines for both groups are outlined below (Figures 2 and 3).

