**Methods:**

Patients with OI type I (the mildest form of OI; n=12, aged 12-16 years) from a pediatric orthopedic tertiary hospital will be randomized to receive a 12-week remote exercise intervention in either (1) a supervised group (n=6), monitored every session, or (2) a follow-up group (n=6), receiving monthly progress update appointments. Participants will undergo the following pre- and postintervention evaluations: sit-to-stand test, push-up test, sit-up test, single-legged balance test, and a heel-rise test. Both groups will be given the same 12-week exercise regimen, which includes cardiovascular, resistance, and flexibility training. For each exercise training session involving the supervised group, a kinesiologist will provide instructions to participants through live video sessions using a teleconferencing application. On the other hand, the follow-up group will discuss their progress with the kinesiologist every 4 weeks over a teleconferencing video call. Feasibility will be assessed by recruitment, adherence, and completion rates. A cost-effectiveness analysis of both approaches will be computed. Changes in muscle function and cardiopulmonary fitness will be examined between the 2 groups, pre- and postintervention.

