### Statistical Analysis

As this is a feasibility study, the testing procedure will be assessed rather than only focusing on the potential outcomes of the intervention. To determine the optimal clinical practice of telemedicine for an exercise intervention, recruitment, adherence, and completion rates of 2 randomized groups (supervised and follow-up approaches) will be investigated. Descriptive statistics will be presented as means and SDs. Based on previous research on home-based exercise interventions [23], the adherence rate will be assessed with a set threshold of 80%. A Wilcoxon rank sum test will be used to evaluate the adherence rate and compare both telemedicine approaches. Whereas both recruitment and completion rates will be compared using descriptive statistics and assessed with a set threshold of 50%. To measure the change in outcome parameters of participants’ muscle strength and cardiopulmonary fitness, pre- and postintervention evaluation results will be assessed with a Friedman ANOVA. A Kruskal-Wallis test will be used to determine the differences in outcome parameter changes between the 2 groups (supervised and follow-up groups).

To assess the cost-effectiveness of the 2 telemedicine approaches, a cost-effectiveness plane and an incremental cost-effectiveness ratio will be computed. The incremental cost and incremental effect will be plotted on a cost-effectiveness plane, where the horizontal axis will represent the incremental cost and the vertical axis will represent the incremental effect [24,25]. The costs and clinical outcomes for both telemedicine groups will be plotted on the plane, which will visually demonstrate the additional cost per unit of health gain for each telemedicine approach. To calculate the incremental cost-effectiveness ratio, the difference in costs will be divided by the difference in mean performance outcomes between the supervised and follow-up groups.

Finally, as OI is classified as a rare disorder [1], analyses will be carried out with a significance level (α) of 0.10 [26]. Statistical analyses will be conducted using the statistical analysis software SPSS, version 25 (SPSS Inc).

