## Discussion

### Overview

The aim of this study is to evaluate the feasibility of 2 telemedicine approaches for the delivery of a home-based exercise program and determine the most cost-effective approach. The secondary aim of the study is to investigate the effect of a home-based exercise program on muscle function and cardiopulmonary fitness in youth with OI type I. Given the aims of the study, it is hypothesized that the supervised group will have higher adherence and completion rates compared to the follow-up group, and therefore, the physiological benefits will be greater in the supervised group than the follow-up group due to additional benefits from constant supervision. However, the follow-up group will receive individual attention in contrast to the supervised group, in which the specialist will work with groups of 3 patients. Direct comparison of patient performance in the supervised and follow-up groups will allow us to identify which telemedicine approach is more cost-effective and efficient for the delivery of an exercise program to OI pediatric patients.

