Greater adherence rates can be associated with benefits such as increased positive reinforcement, improved exercise techniques, and higher self-efficacy [12]. Furthermore, direct supervision is associated with a greater overall volume of exercise achieved and potentially more efficient training, as with this approach, clinicians have the ability to adjust exercises in real time to prevent injury or pain [12]. However, in the follow-up approach, there is schedule flexibility, as participants can perform the intervention sessions when it’s most convenient to them. As well, participants may develop autonomy by completing these sessions independently, which in the long term may lead to long-lasting physical activity as individuals feel more confident in their abilities to exercise on their own. Whereas participants in the supervised group rely on study personnel for instruction and motivation and may not develop the same level of autonomy as individuals in the follow-up group. Although there are several health benefits associated with direct supervision, these advantages may not outweigh the increased cost associated with this approach. Thus, the insight gained from this study into the level of participant supervision necessary for a telemedicine approach to be effective will satisfy the current gap in literature. The results pertaining to the feasibility and cost-effectiveness of both the supervised and follow-up telemedicine approaches will provide clinicians with fundamental knowledge regarding which approach is most feasible for the remote delivery of care to a pediatric and youth population.

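### The supervised arm trains in groups of three and the follow-up arm is seen individually, so an arm difference cannot be credited to supervision level, and the between-arm rank tests ignore the trios

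*Protocol article*

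**What the plan says.** The Abstract (Methods) gives the two arms as "a supervised group (n=6), monitored every session, or (2) a follow-up group (n=6), receiving monthly progress update appointments". The Exercise Intervention section fixes the format of each. For the supervised arm: "Participants in the supervised group will be separated into 2 groups of 3 participants". For the other arm: "For the follow-up group, the kinesiologist will meet with participants individually every 4 weeks". The costing textbox in Results agrees, since it multiplies supervised hours by 2 groups and follow-up hours by 6 participants.

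The Discussion Overview expects that "the physiological benefits will be greater in the supervised group than the follow-up group due to additional benefits from constant supervision". It then notes that one arm gets individual attention and the other works in threes, and goes on to present "the insight gained from this study into the level of participant supervision necessary for a telemedicine approach to be effective" as filling a gap in the literature. The Cost section admits that the group-versus-individual difference makes direct comparison hard, and responds by expressing cost per participant. The Limitations section does not list the difference.

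Under Statistical Analysis: "A Wilcoxon rank sum test will be used to evaluate the adherence rate and compare both telemedicine approaches". Changes in the physical outcomes are compared between arms with a Kruskal-Wallis test, and the significance level is 0.10. The trios are not mentioned.

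**The concern.** Two consequences follow from delivering one arm in trios.

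1. **Attribution.** Supervised participants have both live supervision and the company of two peers. Follow-up participants have neither. No arm has supervision without peers, or peers without supervision. If the supervised arm adheres better or gains more function, exercising with others is as good an explanation as being supervised. A statement about how much supervision is needed is therefore not identified by this design.

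2. **Independence.** The design is partially nested: six supervised participants in two clusters of three, and six follow-up participants with no clustering. Trio members share sessions and peers, so their outcomes may be correlated. The planned rank tests take all 12 observations as independent. If the correlation is positive, the standard error of the arm difference is understated and the true error rate of the test rises.

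At stake are what clinicians are told about supervision and how far a p-value near 0.10 can be trusted.

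**Working it through.** **Inputs.** 12 participants, 6 per arm; supervised arm in 2 trios; α = 0.10 (Abstract, Recruitment, Exercise Intervention, Statistical Analysis). Sidedness is not stated, so two-sided is assumed. The ICC within trios is not given, so it is varied.

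**Reproducing the plan's own figures.** The article has no power calculation, but its costing shows the delivery format:
- Supervised: (8+12+18)×2 groups = 76 h; 76+24 evaluation hours = 100 h; 100×27 = CAD 2700.
- Follow-up: (2+2+2)×6 participants = 36 h; 36+24 = 60 h; 60×27 = CAD 1620.

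Both match. Supervised time is budgeted per trio and follow-up time per person.

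**Attribution.**

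| | Live supervision | Peer group |
|---|---|---|
| Supervised arm | yes | yes (3 per group) |
| Follow-up arm | no | no |

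With two arms and two features that move together, one difference cannot be divided between them. Dividing cost by the number of participants does not change this for adherence or function.

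**Size of the test without clustering.** For 6 v 6 there are 924 equally likely rank allocations, and the mean rank sum is 39. The largest two-sided rejection region with probability at most 0.10 is a rank sum of 28 or less, or 50 or more. Its probability is 86/924 = 0.093. The Kruskal-Wallis chi-square p-value at a rank sum of 28 is 0.078, and that test has the same rejection region, so both planned tests behave alike.

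**Size with trio effects.** Model: equal arm means, normal outcomes, total variance 1 in both arms, and a shared random effect with variance equal to the ICC in each of the two trios. Follow-up participants are independent. There were 300,000 simulated trials per setting.
- Design effect in the supervised arm: 1+(3−1)×ICC = 1+2×ICC.
- Effective supervised sample size: 6/(1+2×ICC).
- Ratio of the true to the independent standard error of the difference: √{[(1+2×ICC)+1]/2} = √(1+ICC).

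| Assumed ICC | Design effect | Effective n (of 6) | SE ratio | Actual size at nominal 0.10 |
|---|---|---|---|---|
| 0 | 1.0 | 6.0 | 1.00 | 0.093 |
| 0.05 | 1.1 | 5.45 | 1.02 | 0.101 |
| 0.1 | 1.2 | 5.0 | 1.05 | 0.109 |
| 0.2 | 1.4 | 4.3 | 1.10 | 0.126 |
| 0.3 | 1.6 | 3.75 | 1.14 | 0.144 |

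Separate simulations agree to within about 0.001 (for example 0.110 at ICC 0.1 and 0.145 at ICC 0.3).

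**Can the analysis simply use the trio as the unit?** Two trio means against six individuals give 28 arrangements (8 choose 2). The smallest two-sided exact p is 2/28 = 0.071, so only the most extreme arrangement could reach 0.10. Two trios also cannot give a usable estimate of the ICC.

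**The case against.** **The aim is a comparison of approaches.** The Objective and the Introduction ask about the feasibility and cost-effectiveness of two telemedicine approaches, and participants are individually randomized. A reader might infer that the format difference invalidates the trial. It does not: the comparison of the two packages as delivered stands. What does not follow is the narrower attribution to supervision.

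**The difference is disclosed, and the study is a pilot.** Both are true, and Limitations warns against strong conclusions. But the warning rests on the small sample, not on format, and the supervision claim is made anyway.

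**The rank test is valid by randomization.** Under the strict null of no effect of any kind, this is right. A reader might infer that the error rate must exceed 0.10. That needs trio-specific effects of some size: the exact test starts at 0.093 and is about 0.101 at ICC 0.05. Nothing in the article points to a different kinesiologist for each trio, and Limitations lets supervised participants make up missed sessions in their own time, which may weaken shared adherence.

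**An unseen analysis plan may handle the nesting.** It may. The article nevertheless names the tests and makes the claim, and both can be qualified there.

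Three further readings are not supported:
- *38 h against 6 h of participant contact.* The textbox gives budgeted kinesiologist time. In month 1 it allows 8 h per trio, while 8 sessions of 35 minutes come to 280 minutes, about 4.7 h.
- *The 21-point adherence gap (89% v 68%) between the two programmes cited in the Introduction.* These differ in disease and in length (16 v 12 weeks), so the gap says nothing about peers or supervision here.
- *The fixed timetable as a further confounder.* Live supervision needs an appointment, so a timetable is part of it. Group format is the separable feature.

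**Conclusion.** The point holds in two parts of unequal strength.

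The attribution part needs no assumption. Supervision and group format are completely aligned with arm in the planned sessions, so the trial can compare group-supervised delivery with individual follow-up but cannot show what level of supervision is necessary.

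The independence part is conditional. If trio-specific effects exist, the size at nominal 0.10 is about 0.11 at ICC 0.1, 0.126 at 0.2 and 0.145 at 0.3, and the standard error of the difference is 5%, 10% and 14% too small relative to the independent one. At ICC 0.05 or below the effect is negligible. These figures assume normal outcomes, equal total variance in the arms and a two-sided test, and the ICC values are not from the documents. The analysis needs a qualification, not replacement.

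**What to change.** **Discussion Overview.** Define the contrast as supervised sessions in groups of three versus individual follow-up every 4 weeks. Remove the claim that the trial will show the level of supervision necessary, and do not ascribe the expected benefit to constant supervision alone.

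**Statistical Analysis.**
- State that the Wilcoxon and Kruskal-Wallis p-values between arms ignore the trios and are descriptive.
- Show supervised results by trio.
- Report the arm difference with an interval whose supervised-arm variance is multiplied by 1+2×ICC over a stated range, for example ICC 0 to 0.3. Use a stated range because two trios cannot estimate the ICC.

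**Cost of the change.** Some rewording and one small sensitivity calculation. Participants, sessions and staffing stay as they are. The downside is a narrower claim and slightly wider intervals (standard error up to 14% larger at ICC 0.3).

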**Figure 2 figure2:**
[figure not shown]
Summary of the 12-week home exercise program for the supervised group. PROMIS: Patient-Reported Outcomes Measurement Information System.

